### Sampling

Like the qualitative methods, FCHVs from each ward will assist in identifying women in the community who fit the eligibility requirements. With their list of names and locations, data collectors will randomly select houses for recruitment. The target sample size is
*n* = 950 (treatment = 475, control = 475) with an anticipated attrition rate of 20%. This was determined by assuming an increase in vaccination rates from 83% (2019 estimate) to 93% (envisioned), an alpha level of 0.05 and power of 80%, and data collection from 6 clusters. To estimate the vaccination rate in Makwanpur in 2019, we assumed an increase of approximately 6% from 2017, when the data were last reported, based on antigen coverage trends from 2014 to 2017 (
Ministry of Health Nepal Department of Health Services, 2018). We estimate an intraclass correlation of 0.01, making the required sample size 380 in the treatment and 380 in the control groups. However, because this is a panel design, we envision an attrition rate of 20%, which brings our sample size at baseline to 950. We will sample four cohorts of women with children younger than one year, women with children between 1–2 years, women who are pregnant at baseline, and prospective mothers. We anticipate greatest availability of women in the first two cohorts, and the least availability of pregnant women, which we expect will create variation in our sample sizes between cohorts. For the complete anticipated sampling breakdown, see
Table 2.

**Table 2. T2:** Breakdown of quantitative data collection by treatment and control facilities.

Participant	Control	Treatment	Total
Women with children <1 year	150	150	300
Women with children 1–2 years	150	150	300
Pregnant women	50	50	100
Prospective mothers	125	125	250
Total	475	475	950

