### Quantitative

The primary objective of the quantitative analysis is to determine whether the Rejoice Architecture intervention results in greater vaccination uptake (or intentions for vaccination) among mothers (or prospective mothers) in the treatment, compared to the control, arm. Hierarchical linear regressions (HLM) will be used to test the primary hypothesis that vaccination rates (number of newborns vaccinated divided by total live births within a catchment area) in the treatment group will be significantly greater (goal is 10 percent) than that in the control group. This analysis will take into account the clustered nature of data within each of the six catchment areas (three in treatment and three in control areas).

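### The stated 80% power at a 5% level treats the between-ward variance as known; with three wards per arm, a valid test of the unadjusted end-line comparison has about 58% power on 4 df

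*Protocol article*

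**What the plan says.** The quantitative Sampling section of the protocol article sets the size by "assuming an increase in vaccination rates from 83% (2019 estimate) to 93% (envisioned"), with "an alpha level of 0.05 and power of 80%, and data collection from 6 clusters". It continues: "We estimate an intraclass correlation of 0.01, making the required sample size 380 in the treatment and 380 in the control groups". Attrition then raises the baseline number: "we envision an attrition rate of 20%, which brings our sample size at baseline to 950", or 475 per arm.

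The quantitative part of Data analysis states: "Hierarchical linear regressions (HLM) will be used to test the primary hypothesis". It adds that "This analysis will take into account the clustered nature of data within each of the six catchment areas", three per arm. It names no reference distribution, degrees-of-freedom method or choice between ML and REML.

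Two design features bear on the point. Under Study setting, each Palika contributes one treatment ward and one control ward, matched on population characteristics. Under Study design in the quantitative methods, the same women are surveyed at baseline and about eight months later. The sample-size text takes no credit for either feature.

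**The concern.** The intervention is applied to wards, so the evidence on its effect comes from differences between wards. An ICC of 0.01 enters the calculation as a fixed inflation of the variance, as if the spread between wards were known. In the analysis that spread must be estimated from six wards, and two arm means use up two of the six degrees of freedom. With 4 df the two-sided 5% critical value is 2.78, not 1.96. A calculation that uses 1.96 therefore states more power than a test holding the 5% level can deliver.

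Two misreadings could follow. A null result might be taken as evidence of no effect because the study is described as having 80% power. If the test itself also used normal quantiles, a nominally significant result would carry more than the stated 5% false-positive risk. The abstract says that the study is meant to inform policymakers, so the stated error rates matter.

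**Working it through.** **Inputs, all from the protocol article.** p1 = 0.83, p2 = 0.93, alpha 0.05, power 80%, ICC 0.01, 380 analysed per arm (Sampling); three wards per arm (Data analysis, Quantitative). Sidedness is not stated. Two-sided is taken, because one-sided versions of the formula give 227 to 293 per arm and do not reproduce 380.

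**1. The plan's own figure.**
- Women per ward: m = 380/3 = 126.7.
- Design effect: 1 + (126.7 − 1) × 0.01 = 2.257.
- Effective n per arm: 380/2.257 = 168.4.
- Variance term: 0.83 × 0.17 + 0.93 × 0.07 = 0.1411 + 0.0651 = 0.2062.
- Standard error of the difference: √(0.2062/168.4) = 0.0350.
- Difference over standard error: 0.10/0.0350 = 2.86.
- Normal-quantile power: Φ(2.86 − 1.96) = 81.5% (80.9% with a pooled variance).

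Solving the same formula for n gives 348 (unpooled) or 363 (pooled) per arm, and about 369 to 375 in variants that round the ward size up. So 380 is a normal-quantile design-effect calculation to within rounding. The attrition step is exact: 380/0.8 = 475, and 2 × 475 = 950.

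**2. Same inputs, between-ward variance estimated.** Replace the normal distribution by a noncentral t with noncentrality 2.86.

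| Analysis | df | 5% critical value | Power |
|---|---|---|---|
| Normal formula | – | 1.96 | 81.5% |
| Unmatched wards (6 − 2) | 4 | 2.78 | 58.0% |
| Palika pairs (3 − 1), matching removes no variance | 2 | 4.30 | 36.2% |

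A pooled variance gives 57.0% on 4 df. With all 475 per arm retained, 4-df power is 62%. With unlimited women in three wards per arm it approaches only about 81%.

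**3. Sensitivity to the ICC, 380 per arm, 4 df.**

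| ICC | Design effect | SE | Noncentrality | Power, 4 df |
|---|---|---|---|---|
| 0.01 | 2.257 | 0.0350 | 2.86 | 58% |
| 0.02 | 3.513 | 0.0437 | 2.29 | 42% |
| 0.05 | 7.283 | 0.0629 | 1.59 | 23% |

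With unlimited women the variance tends to 0.2062 × ICC/3. For 80% power by the normal formula this must not exceed 0.10²/7.849, where 7.849 = (1.96 + 0.84)² with unrounded quantiles. Hence ICC ≤ 3 × 0.01/(0.2062 × 7.849) = 0.0185. Above that, no number of women in three wards per arm gives 80%, even by the plan's own formula.

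**4. Simulation.** Beta-binomial data, three wards of 127 women per arm, ICC 0.01, 40,000 runs per scenario.

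| Test | Rejection rate, both arms 83% | Rejection rate, 83% vs 93% |
|---|---|---|
| Ward-level t, 4 df | 5.0% | 58.4% |
| Linear mixed model, REML, normal quantiles | 9.1% | 79.9% |
| Linear mixed model, ML, normal quantiles | 12.7% | 87.6% |

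The ward-level t test holds its level and confirms the 58%. The normal-quantile tests reach about 80% or more only by exceeding 5% under the null.

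**The case against.** **The type I error is not shown to be a feature of the plan.** A reader might infer that the planned analysis has a 9% to 13% false-positive rate. The document does not support that. It commits to a hierarchical model and says nothing on the reference distribution, which a separate analysis plan may fix with a small-sample method. The range is conditional on a normal-theory test. The power point does not depend on it: a small-sample correction restores the 5% level and leads to the lower power.

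**58% is not the power of the study as such.** It is for an unmatched, unadjusted end-line comparison. If the matching within Palikas is analysed as pairs, 2 df remain, and power is about 36% unless matching removes variance. The repeated survey works the other way. To reach 80% on 4 df, the noncentrality must rise from 2.86 to about 3.76, so baseline adjustment would have to cut the variance to (2.86/3.76)² ≈ 0.58 of its value. That would need a correlation of about 0.65, which is an assumption and not a figure in the protocol. So it would be too strong to say that the design cannot have both 5% and 80%. That holds for the comparison on which the calculation rests, and the Sampling section claims no gain from baseline data or matching.

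**A lower figure for mothers only.** Table 2 lists 300 mothers of children under 2 per arm, and a reader might put 240 per arm (300 × 0.8) into the power calculation. That is an inference, and it leaves out pregnant women who may deliver before end-line. Which cohorts supply the behavioural outcome is a separate question and is not used here.

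**The authors acknowledge six units and limited resources.** They do, under Study setting, but as the reason for not randomising. Limitations does not mention low power or imprecision.

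**Conclusion.** The point holds in this form. The stated 80% power at alpha 0.05 with 380 per arm follows from a formula that takes the between-ward variance as known. At the protocol's own inputs, a valid two-sided 5% test of the unadjusted end-line comparison has about 58% power on 4 df, a shortfall of about 22 points from the stated 80%. A paired analysis on 2 df has about 36% if matching removes no variance. The single ICC of 0.01 carries much of the result: 0.02 gives about 42% and 0.05 about 23% on 4 df.

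These figures assume a two-sided test, equal ward sizes, and no gain from baseline adjustment or matching. The 9% (REML) to 13% (ML) type I error applies only if the hierarchical model is tested with normal quantiles, which the protocol neither states nor excludes. The arithmetic from 380 to 950 is correct; the fault lies in the known-variance assumption behind 380.

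**What to change.** **Analysis text.** Specify a small-sample test of the treatment effect. One option is ward-level summaries, or baseline-adjusted ward-level changes, on a t distribution. The other is the hierarchical model with Kenward-Roger or Satterthwaite degrees of freedom. State whether the Palika pairing is modelled, and set the df to match: 4 between-ward df if unmatched, 2 if analysed as three pairs.

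**Sampling text.** Restate the power as about 58% at 380 per arm and ICC 0.01 (4 df, unmatched, before any gain from baseline adjustment or matching). Name the df assumption, show ICC 0.01 to 0.05 (58%, 42% and 23% at 0.01, 0.02 and 0.05), and give the 2-df paired figure of about 36% beside it. If credit is to be taken for baseline adjustment or matching, state the assumed variance reduction.

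**Reporting.** Make the estimated difference with its small-sample confidence interval the main result.

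**Cost.** No added participants or wards. The change is to wording and analysis choice, at the price of a less favourable stated power. The protocol reports that baseline data are collected and the intervention has not yet been implemented, so the change can be made before end-line data exist.

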### Instruments

Baseline and end-line surveys will measure primary outcomes of immunization behavior and intent to immunize future children. A secondary outcome of general service utilization will also be measured. To assess influencing variables, surveys will measure vaccine knowledge, vaccine attitudes and beliefs, self-efficacy, information sources, and perceived social norms regarding immunization. To understand participants’ experiences and perceptions of their health facilities, surveys will measure quality of communication with providers, past experiences with pregnancy and delivery, and perceptions of their facility’s physical environment. Lastly, the surveys will measure concepts relating to the individual, including their demographics, common methods of communication, interspousal relationships (if married), and mental health. End-line surveys will include all items from the baseline surveys plus an additional section to measure exposure to the intervention.

Surveys will vary slightly depending on the participant’s classification. For instance, mothers of children younger than 2 will receive a survey which includes questions about their immunization behaviors. Conversely, pregnant women and prospective mothers will receive a similar survey that, instead, includes questions about their intentions to immunize their future children and, for some items, requests they answer as if they currently have a child younger than 2. All other survey items will be identical for participants, regardless of their classification.

The Health Facility Checklist will measure the quality of the interior physical environment, exterior physical environment, consultation room, storage and supplies, and accessibility of health facilities. Immunization centers are significantly smaller than health facilities and are only used once per month to provide vaccines. Therefore, the Immunization Center Checklist has been modified to measure the same concepts with only the relevant items. Both checklists use items adapted from the Rapid Assessment Tool (
Scholz *et al.,* 2015) and the Site Assessment for Inpatient Postpartum Care (
JHPIEGO, 2004).

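### The protocol names two primary outcomes, vaccination behavior and intent, but sizes the study and states its primary hypothesis for vaccination only, and no rule orders the two

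*Protocol article*

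**What the plan says.** Quantitative methods, Instruments, states: "Baseline and end-line surveys will measure primary outcomes of immunization behavior and intent to immunize future children". The sentence after it puts general service use in a separate secondary tier, so the plural at the primary level looks deliberate.

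The two outcomes come from different women. In the same section, "mothers of children younger than 2 will receive a survey which includes questions about their immunization behaviors", whereas "pregnant women and prospective mothers will receive a similar survey that, instead, includes questions about their intentions to immunize their future children". Table 2 plans 300 women per arm in the first group (150 + 150) and 175 per arm in the second (50 + 125).

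Data analysis, Quantitative, gives the primary objective as finding out whether the intervention produces "greater vaccination uptake (or intentions for vaccination) among mothers (or prospective mothers) in the treatment, compared to the control, arm". The next sentence is narrower. The hierarchical regressions are there to "test the primary hypothesis that vaccination rates (number of newborns vaccinated divided by total live births within a catchment area") are higher under treatment. Intent does not appear in that hypothesis.

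Sampling derives the study size by "assuming an increase in vaccination rates from 83% (2019 estimate) to 93% (envisioned"), with "an alpha level of 0.05 and power of 80%, and data collection from 6 clusters". It gives no effect size, test or error rate for intent. The Abstract's hypothesis and the third item under Objectives both join behavior and intentions with 'and'.

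**The concern.** A reader of the Instruments section would expect two primary analyses. A reader of the hypothesis sentence would expect one. A reader of the objective could think that a gain in either would do. These imply different success rules, with different error rates and power, and the article does not choose between them.

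The choice affects how the result may be reported. Intent is stated by women who, for some items, answer as if they had a young child. With no order fixed, a rise in stated intent and no change in vaccination could be presented as meeting the primary objective. Equally, a gain in vaccination with no change in intent could be called either a success or a partial failure.

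**Working it through.** **1. The plan's own sample size.** Inputs from Sampling: 83% against 93%, alpha 0.05 (two-sided assumed, as sidedness is not stated), power 80%, ICC 0.01, six clusters (three per arm), attrition 20%.

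- Pooled two-proportion formula, mean rate 0.88: n = [1.96·√(2·0.88·0.12) + 0.842·√(0.83·0.17 + 0.93·0.07)]² / 0.10² ≈ 165 per arm.
- Design effect at 380/3 women per cluster: 1 + (126.7 − 1)·0.01 = 2.257.
- 165 × 2.257 ≈ 372, within 3% of the stated 380. Power at 380 per arm is 80.9%.
- 2 × 380 / 0.80 = 950, as stated.

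The size is therefore accounted for by the vaccination comparison at 0.05. Intent plays no part in it.

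**2. What each section treats as primary.**

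| Section | Behavior | Intent |
|---|---|---|
| Instruments | primary | primary |
| Data analysis, objective | included | included, by 'or' |
| Data analysis, hypothesis | tested (as a vaccination rate) | absent |
| Sampling | powered | absent |

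**3. Error rate under each reading (two-sided 0.05 per test).**

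- Only the stated hypothesis is tested: 5% overall, 2.5% for a false claim of benefit.
- Success required on both, or one combined outcome: at most 5% and 2.5%.
- Both tested, either counts, independent tests: 1 − 0.95² = 9.75%. For false claims of benefit: 1 − 0.975² = 4.94%.

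The groups are different women in the same six clusters, so the tests are not quite independent. With 240 and 140 women per arm at end-line, the standardised variance of an arm mean is 0.01/3 + 0.99/n. That gives 0.00746 for behavior and 0.01040 for intent. If the cluster effects on the two outcomes correlate at c, the test statistics correlate at c·(0.01/3)/√(0.00746·0.01040) = 0.378c. The documents do not give c. For an assumed c of 0.25 to 1, the correlation is 0.09 to 0.38. From the bivariate normal, the overall error is then 9.7% to 9.4%, and the false-benefit error 4.9% to 4.7%.

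**4. Women behind each outcome.**

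- Behavior: 300 × 0.80 = 240 per arm. Design effect 1 + (80 − 1)·0.01 = 1.79; effective size 240/1.79 = 134; power for 83% against 93% is 71%.
- Intent: 175 × 0.80 = 140 per arm. Power cannot be computed, because no effect size is given.
- End-line comes about eight months after baseline, so many women pregnant at baseline will have delivered. The article does not say how they are then classed. If all of them moved to the behavior group (50 × 0.80 = 40 per arm), behavior would have 280 (design effect 1.923, effective size 146, power 75%) and intent 100.

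These powers use the normal approximation, which reproduces the plan's figure. They make no allowance for having only three clusters per arm.

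**5. Cost of splitting alpha instead.** At 0.025 each, the overall error is 1 − 0.975² = 4.94%. Power falls from 80.9% to 72.2% at 380 per arm, and from 71% to 61% at 240.

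**The case against.** The strongest reply is that the inflation is not in the text. The 0.05 is an input to the vaccination calculation, no sentence assigns it to intent, and one primary hypothesis is named. The bracketed 'or' sits in a matched pair and can be read as 'respectively': uptake for mothers, intentions for the others. The Outcomes section supports this, since it describes the items in the same cohort-by-cohort way under one heading. Multiplicity rules are also commonly left to an analysis plan, which is not at hand.

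Most of this stands. A reader might infer that the false-positive rate is in fact nearly doubled, or that success on intent alone is an agreed route to a primary claim. The documents support neither: they never say that either outcome suffices, and a missing multiplicity adjustment is not in itself an error here. Nor can the 140 women per arm for intent be called too few by comparison with 380, because 380 was derived for a different outcome.

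The reply does not remove the inconsistency. Read as 'respectively', the objective still contains two primary comparisons in separate groups, against one hypothesis and one powered outcome. A single combined outcome fits poorly with the plural in Instruments, and no common scale for schedule adherence and intent is described. The conflict lies between sentences that are shown, so it does not depend on an unseen document.

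**Conclusion.** The point holds as an inconsistency about what is primary. Instruments and the primary objective include intent; the sample size and the primary hypothesis do not. The size of the consequence depends on how the gap is filled: 5% if only vaccination is tested, and about 9.4% to 9.75% if both are tested at 0.05 and either counts (false claims of benefit about 4.7% to 4.9% instead of 2.5%). Those upper figures assume two-sided tests, ICC 0.01 and the assumed range of between-outcome cluster correlation. They describe what the wording allows, not what the protocol prescribes.

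One further fact belongs with this point. Whichever rule is chosen, behavior is planned on 300 women per arm at baseline, about 240 after attrition, which gives roughly 71% power under the plan's own assumptions instead of 80%.

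**What to change.** Make Instruments and Data analysis agree. Name vaccination behavior in mothers as the primary outcome, tested at two-sided 0.05, and describe it in the same terms in both places. Make intent in pregnant and prospective women a key secondary outcome, tested in fixed sequence and confirmatory only if behavior succeeds. Remove the bracketed reference to intentions from the primary objective, and align the Abstract's hypothesis and the third item under Objectives.

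In Sampling, state that about 240 women per arm are expected to supply behavior data at end-line, with the resulting power, and that intent has no stated effect size or power. Say how women who deliver between the surveys are classed.

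The fixed sequence costs behavior no power, unlike splitting alpha. The price is that a gain in intent alone can no longer support a primary claim, which narrows a hypothesis the Abstract now gives equal standing. If the investigators want intent to remain primary, requiring success on both would also control the error, at a cost in power. The change is otherwise one of wording. The Contribution section reports baseline data collected and the intervention not yet begun, so it can be made before any end-line data exist.

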### Outcomes

***Immunization behavior and intent.*** Items measuring immunization behavior and intent are adapted from the Nepal Woman Questionnaire from the 2016 Demographic and Health Survey (DHS) and reflect either the degree to which participants have followed the National Immunization Schedule of Nepal (for mothers) or their intent to follow the schedule in the future (for pregnant women and prospective mothers;
Ministry of Health and Population, 2020;
Ministry of Health Nepal *et al.,* 2017).

***General service use.*** Items measuring health service utilization will address how often the participant has visited their health facility in the last three months for common health issues including family planning, pregnancy checkups, Tuberculosis treatment, diarrhea treatment, pneumonia treatment, and child sick visits.

## Data collection

### Training

An in-person training will be held in Kathmandu, Nepal for all data collectors to prepare for the qualitative and baseline assessments. The Principal Investigator will conduct the training alongside research staff from the data collection agency. The training will be held for five days with an objective to prepare the researchers for qualitative and quantitative data collection. Training topics will include key concepts of the study like child health and immunization, techniques for probing in interviews and facilitating focus group discussions, and ethical research conduct. 

Following researcher training, we will pretest all instruments and research methods in one ward in Makwanpur that is not part of the actual study. During pretesting, supervisors will observe and provide feedback on research techniques.

